### Sample size calculation

Sample size calculations are based on the expected effects of the intervention on the main outcome measures concerning quality of care and functional health. In the following sample size calculations we used an alpha of 0.05, power of 80% and inflation of 10% because of anticipated intra-cluster correlation in the homes for the elderly. Regarding health related quality of life, Cohen's D effect size ranged from 0.5 to 3.8 in our meta-analysis [22]. To detect a fair benefit, i.e. effect size = 0.5, a minimum of 64 persons is needed in each group [35]. For functional health and disability we anticipate on a comparable effect-size and consequently identical sample size. Furthermore if we assume a dropout rate of 15% during the 6 months follow-up we need to include at least 100/85 × 64 × 110% = 82 persons in each group.

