#### Cost effectiveness analysis

For the cost-effectiveness analysis the difference in total costs between the intervention and usual care group are compared with the difference over 6 months in improvement of functional health and disability. In addition, a cost utility analysis will be done to assess the incremental costs per Quality Adjusted Life Years (QALY). QALY's are calculated by multiplying the utility based on EuroQol scores [29] with the amount of time a patient spent in this particular health state. Transitions between health states are linearly interpolated.

Uncertainty around the cost-effectiveness and cost-utility ratios is calculated using the bias-corrected percentile method (5000 replications) and presented in a cost-effectiveness plan [39]. The bootstrapped cost and effect pairs will also be used to calculate cost-effectiveness acceptability curves [40].

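### The percentile interval planned for the cost-effectiveness and cost-utility ratios cannot be read if bootstrap effects span zero; the risk is mainly for the cost-utility ratio, and the point is minor

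*Protocol article*

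**What the plan says.** Under Cost effectiveness analysis, the Protocol article defines two ratios. One sets the cost difference against the "difference over 6 months in improvement of functional health and disability". For the other, "a cost utility analysis will be done to assess the incremental costs per Quality Adjusted Life Years (QALY"), with QALYs built from EuroQol utilities: "Transitions between health states are linearly interpolated". Table 1 schedules the EuroQol at baseline and 6 months only.

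For both ratios the article then says: "Uncertainty around the cost-effectiveness and cost-utility ratios is calculated using the bias-corrected percentile method (5000 replications"). The same sentence continues "and presented in a cost-effectiveness plan [39"], evidently the cost-effectiveness plane, and the next one adds: "The bootstrapped cost and effect pairs will also be used to calculate cost-effectiveness acceptability curves".

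Under Cost analysis, the difference in mean costs gets its own bootstrap confidence interval. That quantity can be ordered, so no problem arises there.

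**The concern.** A percentile method sorts the replicates and reads off limits. This works only if a larger value always means the same thing. A cost-effect ratio loses that property once the effect changes sign. It runs off to plus or minus infinity as the effect passes through zero, and a negative ratio can mean cheaper and better or dearer and worse. Bias correction moves the percentiles that are read off; it does not restore the ordering.

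If a material share of replicates has an effect near or below zero, the limits around the ratio have neither their nominal coverage nor a clear meaning. The method is fixed in the text, so this is not a detail left for later. The question is how far this trial is exposed.

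**Working it through.** **Inputs from the Protocol article.** Sample size calculation: effect size 0.5, extended to functional health and disability; 64 per group; 15% dropout; 82 per group; and "we used an alpha of 0.05, power of 80% and inflation of 10% because of anticipated intra-cluster correlation". Design: five homes against five, over 500 residents.

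**Assumed, because the article gives no figure:** baseline/6-month utility correlation ρ of 0.3 to 0.7, equal utility SD at both times, ICC where used, and standardised cost differences.

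**1. The plan's own figure.** A two-sided t-test at 0.05 with 80% power and d = 0.5 needs 63.8, so 64 per group. Then 64 × 100/85 × 1.10 = 82.8, printed as 82. Completers: 82 × 0.85 ≈ 70 per arm. If about 250 per arm are recruited: 250 × 0.85 ≈ 212.

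**2. The effect on the QALY scale.** With two measurements and linear interpolation over half a year, QALY = 0.25 (u0 + u6). Randomised groups share the same expected u0, so the expected difference is 0.25·d·σ, while the SD is 0.25·σ·√(2 + 2ρ). The standardised QALY effect without baseline adjustment is d/√(2 + 2ρ):
- ρ = 0.3: 0.5/√2.6 = 0.310
- ρ = 0.6: 0.5/√3.2 = 0.280
- ρ = 0.7: 0.5/√3.4 = 0.271

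**3. How often replicates cross zero.** Let z = effect/SE, with standardised SE = √(2 × 1.10/n). Averaged over trials, the share of replicates below zero is Φ(−z/√2). The chance that more than 2.5% are below zero is Φ(1.96 − z).

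| Completers per arm | SE | z (ρ = 0.7 to 0.3) | Chance that >2.5% are negative |
|---|---|---|---|
| 70 | 0.177 | 1.53 to 1.75 | 67% to 58% |
| 212 | 0.102 | 2.66 to 3.04 | 24% to 14% |

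At 70 per arm, the average share of negative replicates is 11-14%.

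**4. Coverage of the nominal 95% bias-corrected percentile interval.** Simulation: 1,500 trials of 5,000 replicates, normal cost and effect estimates, correlation −0.1, standardised cost difference −1.25, 0 or 1.25.
- z = 1.58 (70 per arm, ρ = 0.6): 87-91%.
- z ≈ 2.74 (212 per arm, ρ = 0.6, 10% inflation): about 95%.

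A net-benefit interval stays at 94-96%.

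**5. With baseline adjustment.** Take a utility SD of 0.25, ρ = 0.6, 250 per arm and ICC 0.05 (all assumed; about 50 per home). The residual QALY SD is 0.25 × 0.25 × √(1 − 0.36) = 0.05. The SE is 0.05 × √(2/250 × (1 + 49 × 0.05)) = 0.0083. The effect is 0.25 × 0.5 × 0.25 = 0.031, so z ≈ 3.8 and coverage is 95-96%. Under the same assumptions without adjustment, the SD is 0.112, the SE 0.0186, z ≈ 1.7 and coverage about 89-91%.

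**6. The functional health and disability ratio.** Here d = 0.5 applies without dilution. With 212 per arm, the chance that more than 2.5% of replicates are negative is 0.1% at ICC 0, 1% at 0.01, 17% at 0.05 and 38% at 0.10. With 70 per arm it is 16-21% for ICC 0 to 0.01.

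**The case against.** The strongest reply is that the plan already contains the standard remedy. The plane shows the joint distribution, and the acceptability curve gives, at each threshold, the share of pairs with positive net benefit. Both remain valid when effects span zero. This stands and limits the harm. It does not repair the limits themselves, and nothing in the section says when they should be withheld.

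The text also speaks of uncertainty, not of a 95% confidence interval, for the ratios. That is correct as a reading, but a percentile method ordinarily yields limits.

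The Data analysis section plans multivariate adjustment for baseline scores and lists EuroQoL among the outcomes. If this carries over to QALYs, most of the dilution disappears. The economic section does not say that it does.

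A reader might infer that crossing zero is likely in this trial for both ratios, or that coverage would be far below nominal. The documents do not support either. They give no utility SD, correlation, ICC or cost variance. Their only planning effect is d = 0.5, the bottom of the range of 0.5 to 3.8 taken from the authors' meta-analysis. Simulated coverage of 54-77% arises only at assumed effects of 0.2 or 0.1 with ICC 0.05. How the bootstrap should respect homes is a separate clustering question and no part of this point.

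**Conclusion.** The concern holds in a limited form. The named method can give uninterpretable limits, and for a QALY analysis without baseline adjustment at the plan's minimum size this is more likely than not, even under the planned effect of 0.5. The shortfall is modest: about 87-91% coverage instead of 95%. It essentially disappears at about 212 completers per arm with the plan's 10% inflation, or with baseline adjustment at 250 per arm and ICC 0.05. A smaller true effect makes it worse: at d = 0.2, coverage is 86-89% even with that adjustment. For functional health and disability the risk is low unless clustering is strong or recruitment stops near the minimum.

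All coverage figures rest on the assumed correlation, normal estimates and assumed cost differences. With the plane and curves already planned, severity is minor.

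**What to change.** In the Cost effectiveness analysis section, replace the percentile interval on the ratios by incremental net benefit with a bootstrap interval over a stated range of threshold values, computed from the same cost-effect pairs. Report the ratios as point estimates, with the share of pairs in each quadrant, and keep the cost-effectiveness plane and acceptability curves as planned.

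This changes analysis wording only and needs no new data or additional resampling. The small cost is that results must be shown over a range of thresholds instead of as one interval.

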## Discussion

In this paper we described the design of a randomized cost-effective trial of the effect of Disease management on residents of homes for the elderly. This study holds several unique elements. The intervention concerns continuity of care and identification of care needs of the residents. The use of interRAI LTCF enables nurses to accurately diagnose the problems addressed within the complex clinical status of a frail elderly person. As a consequence, primary care physicians will be better informed about the health problems of their patients. This may enable effective disease management. Finally, to persons with complex problems a multidisciplinary consultation is offered by a nursing home physician.

The randomization on level of the homes for the elderly may be a weak point of the design as specific cultural habits of the homes will not be equally distributed over the two groups. On the other hand, randomization of homes will prevent contamination of the intervention to usual care homes.

The implementation of interRAI LTCF demands a great effort on the part of the organization and outcomes are dependent on good use of the instrument.

## Abbreviations

RAI- LTCF Resident Assessment Instrument – Long Term Care Facility; MM Multidisciplinary Meeting; SF12 Short Form 12 item version; QUOTE QUality Of care Through the patient's Eyes; GARS Groningen Activities Restriction Scale; ADL Activities if Daily Living; IADL Instrumental Activities if Daily Living
